**Healthcare economics:**	
Direct costs:	
outpatient care:	hours spent by midwife
	hours spent by obstetrician
	hours spent by administrators
	hours spent by nurse assistants
	physiotherapy
	psychological treatment
	transportation
inpatient care:	length of stay
cost of implementation:	care level
	Information material Information sessions Education Support from the implementation group during implementation Surveillance Equipment for online communication
Indirect cost:	production loss due to healthcare visits

An in-person visit in the MAC study is defined as an in-office visit between a pregnant woman and a midwife for assessing maternal or fetal well-being. Visits solely for e.g. blood sampling are not counted. For virtual meetings, the video-meeting solution adopted by the included ACCs will be used.

If additional visits are called for during pregnancy, e.g. elevated blood pressure, signs of depression, deviating oral glucose tolerance test, follow-up is individualized. The additional visits could be either back to the midwife for closer surveillance, or booked appointments with other health care staff.

#### Development of questionnaires

Two sets of questionnaires have been developed to assess the pregnant women’s and midwives’ views on quality of care and work situation/condition respectively. The questionnaires are called Patient Reported Experience Measures (PREM 1 and 2) and Midwife Reported Experience Measures (MREM 1 and 2). These questionnaires are seen as Supplements 2, 3, 4, 5 in the original language (Swedish). Some of the questions in PREM are inspired by the PREM questions in the Swedish Pregnancy Register. The questions in MREM also reflect these questions but from a caregiver perspective, including questions important for the implementation evaluation. Both PREM and MREM have two versions. Version 1 is designed to measure the status before the implementation of the MAC and version 2 measure these aspects after the implementation. The MREM is used at two time points after the start of the MAC to get feedback from the midwives and if needed to adjust the implementation strategies and/or the program. To ensure the quality of the questionnaires they are validated face-to-face and revised in an iterative process by an expert panel consisting of experienced researchers, health care professionals and responders similar to the target groups.

#### Development of information to the pregnant women and midwives

Information about the upcoming change of the antenatal care program for healthy pregnant women with a low risk for adverse outcomes is developed and planned to be communicated to the general public with the help of the administration for health communication.

The same unit also develops a communication tool for the midwife to use when communicating with the pregnant women about questions that concern the MAC program.

#### Recruitment of antenatal care centers

Six ACCs in the South East region of Sweden with the same SAC program have been informed about the MAC study and five have agreed to participate. They are called ACC A-E in the study. The participating ACCs have approximately 8200 childbirths annually in total.

#### Randomization

A randomization will be performed for the order in which the ACCs will implement the MAC program. A stepped wedge cluster design was chosen to allow participating centers to serve as control and intervention groups respectively [20]. The intervention represents a change in a clinical routine for all pregnant women in the ACCs with the MAC program, making it unrealistic to randomize by individual.

#### Implementation strategies

In order to achieve a successful implementation, the change to the MAC program in each ACC will follow an implementation plan consisting of a step-by step introduction, with a plan-do-study-act design that offers opportunities to evaluate the implementation and, if necessary, facilitate adherence to the program [21–23]. Implementation strategies involve scheduling dialog meetings between research group and midwives where the research group and the midwives could discuss the need for change, trying to reach a common understanding of “why”, and in later meetings “how” and “when” the change will take place. The midwives will have written instructions for the changed routines, and checklists including information about how to get support, both from the research team and the technology department. Further dialog meetings will be held for feedback, to exchange experiences including short- and long-term evaluation, and to resolve needs for improvement of various kinds during the implementation. Additional dialog meetings will also be held when needed.

#### Participants

All pregnant women will be assessed in the first trimester and classified according to risk, see Supplement 1, and eligibility for the MAC program. This will be done by their midwife, with support when needed from senior colleagues and obstetricians.

In this study the definition of healthy pregnant women with a low risk for adverse outcomes eligible for the MAC program is as follows (see supplement 1):Low risk assessment in four dimensions (psychiatric, social, medical and obstetrical health).Low risk in risk assessment for developing preeclampsia. The assessment for the risk of developing preeclampsia is carried out in the first trimester, based on the uterine pulsatility index, medical history, biochemical markers (PLGF, s-hcg PAPP-A) and median blood pressure in both arms. The pregnant women are classified as either low or high risk for preeclampsia before gestational week 37 and 0 days according to this routine [24].Possibility for the pregnant woman to download an app for virtual meetings and use it.Fluent in Swedish or EnglishOn different dates, three of the five ACCs will switch to the MAC program for healthy pregnant women with a low risk for adverse outcomes; the other two will remain as control groups, see Fig. 1.

**Fig. 1 Fig1:**
[figure not shown]
Stepped wedge inclusion. Flow chart of the stepped wedge inclusion of Clusters A-E

#### Data collection and timeline

The first step will consist of educational meetings with the midwives at the participating ACCs, with emphasis on information about why this change would be carried out. Three of the five ACCs (A-C) will be included as controls from study start. The two other ACCs (ACC D-E) will begin as control groups three months after the study start. ACC A will be starting with the MAC program four months after the study start followed by ACCs B and ACC C that will begin the MAC program six and seven months respectively after study start. ACCs D-E will remain as control groups. The first data collection will take place approximately 1.5–2 years after study start.

National registers in Sweden offer a possibility to assess the impact of the MAC program on antenatal, obstetric and neonatal outcomes. Healthy pregnant women with a low risk for adverse outcomes will be registered in the Swedish Pregnancy Register in the first trimester as planned to follow either the SAC or the MAC program. Data will also be extracted from medical records in the Obstetrix^©^ and Cosmic^©^ databases as well as local databases.

During the study period, the pregnant women will receive a web survey around gestational week 37–40, with emphasis on their experience of the given care. Healthy pregnant women with a low risk for adverse outcomes in the SAC program (PREM1, Supplement 2) and the MAC program (PREM2, Supplement 3) will receive the survey. The participating midwives will be given a survey before the start of the MAC program (MREM1, Supplement 4), and at two time points after the start of the MAC program (MREM 2, Supplement 5) (Fig. 2).

**Fig. 2 Fig2:**
[figure not shown]
Flowchart. Flowchart of the Modified Antenatal Care program (MAC) study

#### Quality assurance and monitoring of adhesion to the MAC program

The risk assessment protocol (Supplement 1) has been in use for several years in participating ACCs and has been in use by the midwives since 2016. The risk calculation for developing preeclampsia before gestational week 37 and 0 days [24] is also well established, starting the same year as the risk assessment routine. An evaluation of the 150 first risk assessments in early pregnancy will be scrutinized by a research assistant after the start of the MAC program to ensure that the new routine is applied.

### Outcomes

#### Health

This is a non-inferiority trial with the aim of determining if the MAC program differs in quality and safety compared with the SAC program as regards antenatal, obstetric and neonatal outcomes, including satisfaction of the patient and caregiver. The cost-effectiveness and the implementation of the program will also be assessed. Many outcomes measured in this study are rare, since the MAC program only involves a specific low-risk healthy pregnant population. For this reason, some of the outcomes are clustered in the following composites: antenatal care – measuring the national quality measures of the antenatal care program, obstetric- and neonatal outcomes and health care consumption – measuring frequency and setting of visits. The different outcome composites are listed in Tables 3 and 4.

#### Health economic evaluation

Since this study has a non-inferiority design, it is of great interest to conduct a cost-minimization analysis (CMA) [25, 26]. This will make it possible to determine which program reaches a specified health outcome in a given population for the least cost. This kind of analysis also makes it possible to calculate the costs that would arise if every pregnant woman would receive the same care, opening up discussion about redirecting costs toward patient groups that would need more health care. If the results of the MAC program and the SAC program should diverge significantly, a cost-effectiveness analysis will be carried out instead. In that case, the result will be presented as an incremental cost-effectiveness ratio (ICER), where the additional cost, or potential lower cost, will be put in relation to the difference in effect [27].

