### Sample size and power calculation

The sample size was calculated with a stepped wedge sample size add-on program to Stata. The program can only detect minimum difference between two groups for superiority designs; therefore, the program was used to calculate the minimum difference that can be detected with a given sample size. It was estimated that a minimum of 1500 pregnant women a year will be possible for the MAC program. The average number of pregnancies per month in the clusters will be approximately 46 and was inserted in the program in ten steps, excluding the baseline. This study population will be enough for our primary outcome, the obstetric composite. The minimum detectable difference with a p-value of 5% and 80% power will be larger than what is estimated in the main non-inferiority hypothesis, resulting in the effect size of 4%. The analysis will be based on the principle of intention to treat.

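### The economic plan assumes equal effect unless the programmes differ significantly, so an inconclusive trial would still lead to cost-minimization without non-inferiority having been shown

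*Protocol article*

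**What the plan says.** Under Health economic evaluation, the protocol article bases the choice of economic method on the type of trial: "Since this study has a non-inferiority design, it is of great interest to conduct a cost-minimization analysis". It then gives the one condition for changing method: "If the results of the MAC program and the SAC program should diverge significantly, a cost-effectiveness analysis will be carried out instead". In that case an incremental cost-effectiveness ratio is to be reported. The section mentions no margin and no confidence limit, and does not say which outcome the results are.

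Outcomes, Health describes the framework: "This is a non-inferiority trial with the aim of determining if the MAC program differs in quality and safety compared with the SAC program". The same section says that many outcomes are rare in this low-risk population and that cost-effectiveness will be assessed.

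Sample size and power calculation names the primary outcome: "This study population will be enough for our primary outcome, the obstetric composite". It explains that the software covers superiority only ("The program can only detect minimum difference between two groups for superiority designs") and then states: "The minimum detectable difference with a p-value of 5% and 80% power will be larger than what is estimated in the main non-inferiority hypothesis". The figure given for that detectable difference is 4%.

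**The concern.** Two questions are being treated as one. A significance test asks whether the data exclude a zero difference. A non-inferiority test asks whether they exclude a difference as bad as the margin. A wide confidence interval can exclude neither, and such a result is inconclusive. The stated rule sends it to cost-minimization, where the effect difference is set to zero. The less precise the trial, the likelier this becomes.

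The rule can also err the other way. A significant difference lying wholly inside the margin would remove cost-minimization although non-inferiority had been shown.

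Lower cost of the modified programme is one of the stated hypotheses, and the economic result is meant to inform a shift of resources to women with greater needs. A finding that the modified programme is cheaper at equal effect should not rest on a lack of power. The rule is written out in the article, so this is not a detail left to an analysis plan.

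**Working it through.** **Inputs from the article** (Sample size and power calculation): detectable difference 4%, significance level 5%, power 80%, about 46 pregnancies per month, ten steps plus baseline.

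**Assumptions:** a two-sided 5% level; 4% read as percentage points; non-inferiority judged by the upper 95% confidence limit for the excess risk under the modified programme; margin M of 2 to 5 points, because none is printed.

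**1. Can the 4% be reproduced?** The article gives neither an event rate nor an intracluster correlation (ICC), so it can be neither confirmed nor refuted. In a standard stepped-wedge (Hussey-Hughes) variance with ten steps, one cluster per step and 46 women per cluster-month, and with ICC 0.001 to 0.05, the detectable difference is:
- 2.4 to 2.9 points at a 5% event rate;
- 3.3 to 4.0 points at 10%;
- 3.9 to 4.7 points at 15%.

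So 4% is attainable under plausible inputs. It is used below as stated.

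**2. Implied precision.**
- Standard error = 4 / (1.960 + 0.842) = 1.43 points.
- 95% confidence half-width = 1.960 × 1.43 = 2.80 points.

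**3. Where the two rules disagree.** Let d be the observed excess under the modified programme. The result is non-significant if −2.80 < d < 2.80. Non-inferiority is shown if d + 2.80 < M. For the margins used here, the stated rule keeps cost-minimization without shown non-inferiority when M − 2.80 < d < 2.80. For M = 4, that is any observed excess between 1.20 and 2.80 points.

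**4. How often this happens.** For a true excess δ, the probability is Φ((2.80 − δ)/1.43) − Φ((M − 2.80 − δ)/1.43).

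| Assumed margin M | Range of d | δ = 0 | δ = 2 |
|---|---|---|---|
| 2 | −0.80 to 2.80 | 69% | 69% |
| 3 | 0.20 to 2.80 | 42% | 61% |
| 4 | 1.20 to 2.80 | 17.5% | 42% |
| 5 | 2.20 to 2.80 | 4% | 16% |

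Example, M = 4 and δ = 2: Φ(0.56) − Φ(−0.56) = 0.712 − 0.288 = 0.424.

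**5. True harm equal to the margin.** Non-inferiority is then shown in 2.5% of trials, but the difference is non-significant, and cost-minimization is kept, in 71% (M = 2), 44% (M = 3) or 20% (M = 4).

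**6. The reverse error.** For harm to be significant yet inside the margin, both d > 2.80 and d + 2.80 < M must hold, so M must exceed 2 × 2.80 = 5.60 points. At this precision the reverse error does not arise for margins of 2 to 5 points. It would arise with a wider margin or a more precise estimate. Below 5.60 points the inconclusive zone of step 3 is always present.

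**The case against.** **The wording is looser than a significance test.** The section names no test, level or outcome, and its trigger could mean any important divergence, including failed non-inferiority. It is fair to say that the trigger is undefined. This does not rescue the rule: on the looser reading, too, cost-minimization is the default by virtue of the design and does not require shown non-inferiority.

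**The size depends on assumptions.** This stands. The margins are assumed, and the probabilities run from 4% to 69%. The article does say that the detectable difference exceeds what its non-inferiority hypothesis estimates. If that refers to the margin, the margin lies below 4 points, where the problem is larger, but the sentence is too unclear to rely on.

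**A stronger number is tempting but not supported.** A reader might infer a definite failure rate for the actual rollout. With a 10% event rate, ICC 0.01 to 0.05, 46 women per centre-month and 21 months, a true 4-point harm would be non-significant in about 44% to 54% of trials. The article does not give the event rate, the ICC or a 21-month analysis period. The 46 is itself uncertain, since 1500 women a year over five centres is 1500 / 12 / 5 = 25 per centre-month. Over event rates of 5% to 20%, ICC 0.001 to 0.05 and 25 to 46 per centre-month, the same 21-month calculation runs from about 1% to 81%. It also measures the wrong event: a missed 4-point difference, not a non-significant result that fails non-inferiority.

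**Uncertainty in the economic result.** A reader might infer that the plan ignores uncertainty about effect. The article does not say so, and its handling can properly be left to an analysis plan. Nor does the defect by itself require cost-effectiveness planes or acceptability curves.

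**The economic evaluation is not the primary outcome.** This is true. The rule does not alter the safety conclusion on the obstetric composite.

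**Conclusion.** The concern holds as a fault in a stated decision rule. Cost-minimization is justified by the trial's design rather than by its result, and it is dropped only on a significant divergence. An inconclusive trial would be analysed as if the programmes were equally effective. This conclusion is a matter of logic and does not depend on the event rate, the ICC or the margin.

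The size is illustrative. It rests on the stated 4%, 5% and 80%, a two-sided level, percentage points and an assumed margin. For margins of 2 to 4 points the affected share of trials is substantial, at 17.5% to 69% with no true difference and 42% to 69% with a 2-point excess. At 5 points it falls to 4% and 16%. No single probability for the actual five-centre rollout can be derived from the article.

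The rule should be changed before the economic analysis is done, because its conclusion is intended to inform resource allocation.

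**What to change.** Replace the trigger. Present cost-minimization only if the confidence limit for the primary obstetric composite meets the pre-specified non-inferiority criterion, and name that outcome and criterion in the economic section. Otherwise, and preferably in all cases, report incremental cost and incremental effect jointly with their uncertainty, both estimated from the same centre- and period-adjusted models.

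This takes a short change of text and some extra analysis of cost and outcome data already planned for collection (Tables 3 and 4). No new data are needed. The drawback is that an inconclusive trial will no longer give a simple statement that one programme is cheaper at equal effect, which it could not support in any case.

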### Sample size and power calculation

The sample size was calculated with a stepped wedge sample size add-on program to Stata. The program can only detect minimum difference between two groups for superiority designs; therefore, the program was used to calculate the minimum difference that can be detected with a given sample size. It was estimated that a minimum of 1500 pregnant women a year will be possible for the MAC program. The average number of pregnancies per month in the clusters will be approximately 46 and was inserted in the program in ten steps, excluding the baseline. This study population will be enough for our primary outcome, the obstetric composite. The minimum detectable difference with a p-value of 5% and 80% power will be larger than what is estimated in the main non-inferiority hypothesis, resulting in the effect size of 4%. The analysis will be based on the principle of intention to treat.

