Our hypothesis is that the modified antenatal care (MAC) program does not differ in regard to antenatal, obstetric and neonatal outcomes compared to the SAC program. We also hypothesize that the cost of the MAC program is lower than the cost of the SAC program. We also assume that selected implementation strategies will support a high level of adherence and sustainability for the MAC program.

This study protocol will describe the guideline development of a MAC program. The study design and methods aimed to investigate if a reduction in-person visits to a midwife with some of those visits replaced with virtual visits is safe for healthy pregnant women with a low risk for adverse outcomes. The planned study will evaluate a MAC program in comparison to the SAC program for healthy pregnant women with a low risk for adverse outcomes, considering the following aspects: maternal- and neonatal outcomes, patient- and caregiver-reported experiences, healthcare economy, and will also evaluate the MAC program implementation.

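### The sample is called sufficient although the detectable difference is said to exceed what the non-inferiority hypothesis estimates, and no margin is stated to settle the matter

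*Protocol article*

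**What the plan says.** All references are to the protocol article.

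- **Sample size and power calculation.** A superiority-only stepped wedge program was used to find the difference detectable with a given sample. On adequacy: "This study population will be enough for our primary outcome, the obstetric composite". The next sentence reads "The minimum detectable difference with a p-value of 5% and 80% power will be larger than what is estimated in the main non-inferiority hypothesis", and it ends "resulting in the effect size of 4" per cent. The scale of the 4%, the sidedness of the 5%, the control event rate and the intracluster correlation are not given.
- **Background.** "Our hypothesis is that the modified antenatal care (MAC) program does not differ in regard to antenatal, obstetric and neonatal outcomes" compared with the standard program (SAC).
- **Outcomes, Health.** "This is a non-inferiority trial with the aim of determining if the MAC program differs in quality and safety" compared with SAC.
- **Health economic evaluation.** Because the design is non-inferiority, a cost-minimization analysis is planned. A cost-effectiveness analysis replaces it only if the two programs' results differ significantly.

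No section gives a non-inferiority margin. The 4% is labelled an effect size.

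**The concern.** A sample is enough for a hypothesis when the difference it can detect, or rule out, is no larger than the one the hypothesis concerns. Here the detectable difference is said to be the larger of the two, yet the sample is called sufficient. The article prints only one side of the comparison (4%), so the reader cannot resolve the conflict.

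The loose wording elsewhere adds to the problem. A hypothesis of no difference, an aim of finding whether the programs differ, and an economic rule triggered by a significant difference all point to a significance test. None points to a bound on how much worse the modified program (MAC) may be. In a trial that cuts in-person midwife visits from eight to four, an imprecise result without a significant difference could then be carried into the safety and cost conclusions as if it showed equivalence.

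**Working it through.** **1. Can the 4% be reproduced?** Not uniquely, because the control rate and intracluster correlation (ICC) are missing. I used the Hussey–Hughes variance (random cluster effect, fixed period effects) and detectable difference = (1.960 + 0.842) × SE, over assumed control rates of 5–50% and ICC of 0–0.05.

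| Layout | Assumed control rate, ICC | Detectable difference |
|---|---|---|
| Ten steps, one cluster per step, 46 per cluster-month | 20%, 0 | 4.07% |
| same | 15%, 0.001 | 3.94% |
| same | 10%, 0.01 | 3.86% |
| same | all values tried | about 2.2% to 6.6% |
| Five centers, switches after 4, 6 and 7 months, two centers staying control, 46 per cluster-month, 24 months | all values tried | 1.9% to 9.9% |

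So 4% is attainable under some assumptions and is not shown to be wrong. I take it as given below.

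**2. From detectable difference to margin.** Assume that 4% means absolute percentage points, that the 5% is two-sided, and that the true risks are equal.

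- Implied SE = 4 / (1.960 + 0.842) = 4 / 2.802 = 1.428 points.
- Power to rule out a margin m = Φ(m / 1.428 − z), with z = 1.960 for a one-sided 2.5% test and z = 1.645 for a one-sided 5% test.

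| Assumed margin (points) | One-sided 2.5% | One-sided 5% |
|---|---|---|
| 4.0 | 80.0% | 87.6% |
| 3.5 | 68.8% | 79.0% |
| 3.0 | 55.6% | 67.6% |
| 2.0 | 28.8% | 40.4% |
| 1.0 | 10.4% | 17.2% |

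With a one-sided 2.5% test, 80% is reached only at 4 points. With a one-sided 5% test it is reached at (1.645 + 0.842) × 1.428 = 3.55 points. The margins are illustrations, because the article gives none.

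**3. The possible readings of the sentence.**

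- *The hypothesised quantity is the margin.* It is then below 4%. With a one-sided 2.5% test, power is below 80% and the sample is not enough in the stated sense.
- *It is the expected difference, near zero.* Every detectable difference exceeds zero, so the comparison says nothing about adequacy and the claim of sufficiency has no support.
- *4% is itself the margin.* The detectable difference then equals the hypothesised value, and calling it larger is wrong.
- *The superiority calculation is meant as conservative.* Sufficiency then holds for margins between about 3.55 and 4 points, and only with a one-sided 5% non-inferiority test. The article states neither the margin nor such a test.

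**The case against.** The strongest reply is that the sentence is ambiguous and never uses the word margin. A reader might infer that the trial is proven to be underpowered for its own hypothesis. The text does not support that. The shortfall follows only if the hypothesised quantity is the margin and the test is one-sided 2.5%. Under the expected-difference reading, or the conservative reading with a margin of about 3.55 to 4 points, no shortfall is shown. This part of the reply stands, and the power figures above are conditional illustrations.

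A reader might also infer that power is lower still under the layout actually described, in which only three of five centers switch. That is not shown here: the range of 1.9% to 9.9% lies on both sides of 4%.

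A third inference would be that the team will count non-significance as success or choose the margin after seeing the data. The article says neither. It repeatedly names a non-inferiority design and refers to an existing main hypothesis, and the full protocol and analysis plan are not shown. What holds is weaker: the wording permits a non-significant difference to be taken as equivalence.

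Finally, an article may leave details to fuller documents. That does not dispose of the point. The article makes a claim of adequacy that rests on a comparison with the hypothesis, and the comparison as printed does not support the claim.

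**Conclusion.** The point stands in conditional form. The sufficiency claim and the sentence after it conflict on the plain reading. On the alternatives, the claim is unsupported, or the comparison is wrong, or the claim holds only under a margin and test that are not stated. Correction is needed whichever was meant.

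The size of any shortfall cannot be fixed without a margin, and the figures in the working rest on its assumptions about scale, sidedness and true equality. That the article gives no margin, and that the hypothesis, aim and economic rule are phrased in terms of difference, can be read directly from the text and does not depend on those assumptions.

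**What to change.** Before the first data extraction:

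1. State the non-inferiority margin for the obstetric composite, with its scale (absolute or relative) and the sidedness of the test.
2. Conclude non-inferiority only if the corresponding confidence limit for MAC versus SAC excludes that margin.
3. Tie the choice between cost-minimization and cost-effectiveness analysis to the same criterion, in place of a significant difference.
4. Restate the power at that margin, and limit the claim of sufficiency to margins for which 80% holds: about 4 points if tested at one-sided 2.5%, taking the 4% as given.
5. Reword the hypothesis and the aim to say that MAC is not worse than SAC by more than the margin.

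The cost is a change of wording in the protocol or analysis plan and probably a less favourable power statement. No extra women are needed.

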**Methods:**

This is a non-inferiority trial where a stepped wedge cluster randomized controlled design will be used. Data collection includes register data and questionnaires that concern antenatal, obstetric and neonatal outcomes, patient- and caregiver-reported experiences, healthcare-economy, and implementation aspects. The modified antenatal care (MAC) study is performed in parts of the southeast of Sweden, which has approximately 8200 childbirths annually. At the start of the study, all antenatal care centers included in the study will use the same standard antenatal care (SAC) program. In the MAC program the in-person visits to a midwife will be reduced to four instead of eight, with two additional virtual meetings compared with the SAC program.

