## Methods

### Study design

This is a stepped wedge cluster randomized controlled trial comparing two different programs: the standard antenatal care (SAC) program and the modified antenatal care (MAC) program in five antenatal care centers (ACC) where each participating ACC constitutes one cluster (A-E). All visits to both the SAC and MAC take place in an ACC in the South East region of Sweden. At the start of the study, all ACCs will use the same and current SAC program. The healthy pregnant women with a low risk for adverse outcomes, who are attending the current SAC program will constitute the control group. After the start of the MAC program, the corresponding women will constitute the index group.

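### The sample is called sufficient for the primary outcome on the strength of a 4% superiority detectable difference that the text never ties to a non-inferiority margin

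*Protocol article*

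**What the plan says.** The abstract of the protocol article sets the aim: "This is a non-inferiority trial where a stepped wedge cluster randomized controlled design will be used".

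The section on sample size and power makes these statements, in this order:

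- The Stata add-on has a limitation: "The program can only detect minimum difference between two groups for superiority designs". It was therefore used to find the smallest difference detectable with the women available.
- On numbers: "a minimum of 1500 pregnant women a year will be possible for the MAC program". About 46 pregnancies per month and ten steps after baseline were entered.
- On adequacy: "This study population will be enough for our primary outcome, the obstetric composite".
- On the result: "The minimum detectable difference with a p-value of 5% and 80% power will be larger than what is estimated in the main non-inferiority hypothesis". The same sentence then gives an effect size of 4%.

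The article prints no numerical margin, control event rate, intracluster correlation or sidedness for the 5%. The Background states the hypothesis only as an absence of difference between the programs. Whether the 4% is absolute or relative is not stated.

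**The concern.** In a non-inferiority trial, power is the chance that the confidence limit excludes the margin. A sample is large enough when the difference detectable at the chosen power is no larger than that margin. Here the detectable difference is said to be larger than the difference in the non-inferiority hypothesis, and the sample is still called sufficient. On its plain reading that gives the reason for doubting the sample as the reason for accepting it.

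The adequacy claim concerns the primary outcome of a trial that halves in-person midwife visits from eight to four. The section on health outcomes words the non-inferiority aim as finding out whether the programs differ. The health economic section makes cost-minimization the default unless results diverge significantly. With that wording, an inconclusive comparison could be taken as support for the reduced program, so the reader needs to know what the stated 80% refers to.

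**Working it through.** **1. Can the 4% be reproduced?** No, because the control rate and intracluster correlation are not given. A Hussey-Hughes variance (exchangeable correlation, binomial variance) with detectable difference = (1.960 + 0.842) × SE was run over assumed control rates of 5-50% and correlations of 0-0.1. It used the article's 46 women per cluster-month.

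- Standard ten-step layout, one cluster per step (assumed): 2.2 to 6.6 points.
- Layout described in the article ("three of the five ACCs will switch to the MAC program", at months 4, 6 and 7, with the other two centers joining at month 3 and staying on control): 3.3 to 11.4 points over 11 months and 1.9 to 9.9 over 24 months.

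Four points lies inside all three ranges, so the figure is neither confirmed nor refuted. It is taken at face value below.

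**2. Standard error implied by the 4%.** Assumptions: 4% means percentage points, and the 5% is two-sided.

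SE = 4 / (1.960 + 0.842) = 1.428 points.

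**3. Non-inferiority power.** Assumption: no true difference between programs.

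Power = Φ(margin / SE − z), with z = 1.960 (one-sided 2.5%) or 1.645 (one-sided 5%).

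| Margin (points) | Margin / SE | Power, one-sided 2.5% | Power, one-sided 5% |
|---|---|---|---|
| 4.0 | 2.802 | Φ(0.842) = 80% | Φ(1.157) = 88% |
| 3.5 | 2.451 | Φ(0.491) = 69% | Φ(0.806) = 79% |
| 3.0 | 2.101 | Φ(0.141) = 56% | Φ(0.456) = 68% |
| 2.0 | 1.401 | Φ(−0.559) = 29% | Φ(−0.244) = 40% |

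**4. Smallest margin with 80% power.**

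- One-sided 2.5%: 1.428 × (1.960 + 0.842) = 4.0 points.
- One-sided 5%: 1.428 × (1.645 + 0.842) = 3.55 points.

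At one-sided 2.5%, 80% power would need (4/3)² = 1.8 times the information for a 3-point margin and (4/2)² = 4 times for a 2-point margin.

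**5. The possible meanings of the hypothesis difference.**

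- *It is the margin.* The margin is then below 4 points, and power at one-sided 2.5% is below 80% for every such value. At one-sided 5%, margins from 3.55 up to 4 points would still keep 80%.
- *It is the expected true difference, near zero.* A detectable difference above it only makes a non-significant superiority test likely. That is not power to exclude a margin.
- *The superiority figure is meant as conservative against a one-sided 5% test.* The sentence is then coherent (4.0 against 3.55), but 80% power holds only if the margin is at least 3.55 points, which the text does not say.

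**6. The software limitation.** With no true difference, a two-sided 5% superiority calculation with the margin entered as the difference gives the one-sided 2.5% non-inferiority answer, apart from a small variance effect for a binary outcome. The add-on could therefore have been used to power on the margin.

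**The case against.** The strongest defence is that the sentence is ambiguous rather than wrong. It follows a statement that the program handles only superiority, so it can be read as saying that the superiority figure is larger, hence safer, than a non-inferiority calculation would give. On that reading the adequacy statement and the comparison agree. By the equivalence in step 6, a 4-point detectable difference at 80% power is also 80% non-inferiority power for a 4-point margin, so the 80% does apply to one non-inferiority question. No printed number has been shown to be wrong. The article condenses a fuller protocol, and the margin may well stand there or in the analysis plan.

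Most of this stands. A reader might infer that the paragraph flatly contradicts itself and that the trial is underpowered. The text does not establish that, because it does not say that the hypothesis difference is the margin. A reader might also infer that the number of available women, and no clinical judgement, supplied the only threshold. The reference to a main non-inferiority hypothesis suggests that a separate value may exist, so the article does not support that inference either. Nor is the absence of a printed margin or decision rule a fault in itself.

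The defence does not rescue the adequacy claim as written. None of the three meanings connects the 80% to the trial's own margin, and the most literal one counts against the claim.

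**Conclusion.** The point holds in a limited form. The statement that the sample suffices for the primary composite is unsupported as written: it rests on a 4% superiority figure whose stated relation to the non-inferiority hypothesis is either unfavourable or unclear. Eighty per cent non-inferiority power is shown only for a margin of about 4 points at one-sided 2.5%, or at least 3.55 points at one-sided 5%.

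The possible loss runs from none, if the margin is 4 points, to power of 29% (one-sided 2.5%) or 40% (one-sided 5%) if it is 2 points. Which applies cannot be told from the article. The figures assume an absolute 4%, a two-sided 5% and no true difference. If the 5% was one-sided, SE becomes 4 / (1.645 + 0.842) = 1.61 points and every power in the table falls. Power would also be lower if the modified program is truly somewhat worse.

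**What to change.** - Correct the sentence to say what the 4% is: absolute or relative, and one- or two-sided 5%.
- Enter the margin of the main hypothesis, as fixed before outcome data are opened, as the difference in the stepped-wedge routine. Report the resulting power with its one-sided level.
- Withdraw the statement that the population suffices if that power is below 80%.
- Do not use the 4% detectable difference as the margin unless 4% is the margin that was pre-set.

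The cost is a rewritten paragraph and one rerun of the program. The stated power may become less favourable. No extra women are needed for this change.
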